### 2.6. Sample size and data analysis

Although sample size calculations are not necessary for observational registry studies, we have determined that 420 individuals are needed, considering the volume of business at the outpatient clinics taking part in this study.

Each outcome measure will be compared to the clinical outcome between the baseline and termination, and the clinical outcome will be a dependent variable. Combinations of the applied acupoints will act as independent factors to predict the most effective acupoints for the acupuncture treatment. To improve the effectiveness of acupuncture treatments for FGID patients, the properties of the acupoints will be extracted using machine learning algorithms, such as support vector machine and logistic regression models.

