### 2.2. Study design

Up to 420 patients with a doctor-diagnosed FGID will participate in this multi-center, prospective observational registry study. This study will be conducted in 15 traditional Korean medical clinics located in the Republic of Korea. All subjects will be recruited from the daily outpatient department of each clinic participating in the study.

First, using various methods of pattern identification, we will investigate the acupoint selection patterns that doctors recommend for patients with FGIDs. Patients with FGIDs will receive a pattern identification questionnaire. Second, we will determine which acupoints are best for treating FGID. A machine learning method will be used to extract the combinations of acupoints to predict the acupuncture responders. Patients included in the study will complete a series of questionnaires a maximum of 3 times throughout their treatment period: at the first appointment (week 0), 2 weeks later (week 2), and 4 weeks later (week 4).

After receiving an explanation of the advantages and disadvantages of participating in the study, the patients will be requested to sign an informed consent form in writing during their initial appointment. They will be assessed for compliance with the inclusion and exclusion criteria in a screening procedure. Eligible subjects will be added to the registry after screening. The patients will receive combined Korean medical treatment for a maximum of 4 weeks, which will include acupuncture treatment and the responses to a series of questionnaires. The detailed study procedure is shown in Figure 1.

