#### 2.4.1. Acupuncture treatment.

Based on the top 10 frequently used acupoints according to previous systematic reviews, examples of acupoints (e.g., CV12, ST25, ST36, CV10, LR3, BL20, PC6, GV7, BL21, and SP6) will be shown in the case report form. Pattern identification will be used to choose the acupoints, and more acupoints will be permitted based on the patient additional symptoms. There will be no restrictions on the number of acupoints used for treatment. Korean medical experts with at least 5 years of clinical practice will deliver all acupuncture treatments.

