## 3. Discussion

This study will collect clinical data from 15 multicenter Korean medical clinics that treat FGID as part of an observational study registry. With a machine learning system, we will further determine the best acupoints for treating FGID patients after analyzing the acupoint selection patterns.

Depending on the pattern, multiple acupuncture treatments for the same disease may be suggested by traditional Korean medicine. In a previous study, 69 Korean clinicians were asked to provide diagnoses for hypothetical patients based on the clinical information from a previous study that employed a traditional Korean medicine diagnostic algorithm.^[10]^ The most often used acupoints for individuals with FD were CV12, LI4, LR3, ST36, and PC6 but the choices varied depending on which of the 3 patterns (liver qi depression, spleen-stomach weakness, and food accumulation/phlegm-fluid retention) was present. Ha^[13]^ created a 36-item test for studying functional dyspepsia (STPI-FD) based on the Delphi technique and the opinions of specialists, and from which 6 types of FD were distinguished: spleen and stomach deficiency and cold, spleen deficiency with qi stagnation, liver-stomach disharmony, tangled cold and heat pattern, dampness and heat in the spleen and stomach, and food retention pattern. Depending on the pattern identified, supervised learning will be used to extract important clinical features. For our proposed study, we anticipate that the data collected from the 15 different clinics will reveal various FGID patient patterns and further illustrate the patterns of the chosen acupoint combinations. To identify the optimum acupoints for disorders such as FGID, pattern identification based on supervised learning will be used to extract crucial information from real-world clinical data.

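### The plan commits to naming the most effective acupoints, but its only stated validation scores patient classification and cannot show that any acupoint outperforms the others

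*Protocol article*

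**What the plan says.** The aim of finding the best acupoints appears in the Introduction, in sections 2.2 and 2.6, and twice in section 3. Section 2.2 says "A machine learning method will be used to extract the combinations of acupoints to predict the acupuncture responders". Section 2.6 makes acupoint combinations the predictors: "Combinations of the applied acupoints will act as independent factors to predict the most effective acupoints for the acupuncture treatment". It then says "the properties of the acupoints will be extracted using machine learning algorithms, such as support vector machine and logistic regression models". Section 3 says "With a machine learning system, we will further determine the best acupoints for treating FGID patients after analyzing the acupoint selection patterns".

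On the candidates, section 2.4.1 says "examples of acupoints (e.g., CV12, ST25, ST36, CV10, LR3, BL20, PC6, GV7, BL21, and SP6) will be shown in the case report form", allows further points, and adds "There will be no restrictions on the number of acupoints used for treatment".

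On size, section 2.2 says "Up to 420 patients with a doctor-diagnosed FGID will participate in this multi-center, prospective observational registry study" and section 2.6 says "we have determined that 420 individuals are needed, considering the volume of business at the outpatient clinics taking part in this study".

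On validation, section 3 trains the model on 80% of the FD patients and tests it on the other 20%, using accuracy, sensitivity and specificity. A responder is a patient with a minimal clinically significant improvement after 4 weeks. No performance level is set. Nothing in the article says what evidence would make an acupoint effective, or that the answer may be that none stands out.

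**The concern.** The stated conclusion and the stated check concern different things. The conclusion is comparative: some acupoints work better than others. The check asks whether a model sorts patients into responders and non-responders. A model can do that for reasons unrelated to acupoints. Section 3 itself reports that in an earlier support vector machine study of FD the significant predictors were gender, disease subtype and education level. If such variables enter this model, it could validate well while every acupoint is inert.

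Any fitted model also has features that look most favourable. With no criterion separating them from chance, a statement about the best acupoints can be written whether or not acupoints differ. That statement is the study's second aim, and section 3 expects it to guide the choice of points for individual patients. The problem would remain with perfect adjustment for confounding and with independent patients.

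**Working it through.** **Plan's own figures.** The 420 rests on clinic volume, and the article gives no statistical inputs, so no formula reproduces it. If all patients had FD, the split would be 0.8 × 420 = 336 for training and 0.2 × 420 = 84 for testing. These are upper limits, because patients with irritable bowel syndrome are also enrolled.

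**Candidates.** The ten printed points alone give 2^10 − 1 = 1,023 non-empty sets and 10 × 9 / 2 = 45 pairs. More points are allowed. The article does not say whether combinations enter as whole sets or as one indicator per point.

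**Assumptions for the null simulations (none is in the article).** Response does not depend on acupoints, and points are used independently.
- Single points and whole sets: responder rate 30%, 50% or 70%; use rates mixed (5–90%), all 50%, or skewed (2–95%); N = 420 or 336; 600 data sets per setting.
- Pairs: use rates 15–80%; responder rate 50% or 70%; N = 420, or 210 if half have FD; 80% training; pairs with at least 10 users; 2,000 data sets per setting.

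**Single points, additive logistic model.** At least one coefficient is positive in 99.8–100% of data sets. This is close to arithmetic: for ten symmetric, independent null coefficients, 1 − 2^−10 = 99.9%. The size of the leading effect says more:

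| Use pattern | N | Median odds ratio of top point (truth 1) |
|---|---|---|
| All 50% | 420 | 1.34 |
| Mixed | 420 | 1.52–1.59 |
| Mixed | 336 | 1.62–1.71 |
| Skewed | 420 | 1.90 |

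**Pairs.** Gain = responder rate in users of both points minus the rate in all others.

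| N | Best pair, training | Same pair, hold-out | Any pair with z > 1.96 |
|---|---|---|---|
| 420 | 16–18 points | about 0 (−1 to +1) | 49–51% |
| 210 | 20–22 points | about 0 (−1 to +1) | 45–50% |

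**Whole sets ranked on raw response (N = 420, no minimum count).** Between 65 and 345 distinct sets occur, depending on the use pattern. The median top set has one user and 100% response. It is at or below the median use in 73–91% of data sets. This pull depends on how the points are coded. With single-point indicators and no penalty, the rarest point leads in 18–25% of data sets under unequal use (10% if all were equally likely), but near-universal points also lead in 10–17% each. With a ridge penalty the shares are 6–14%. With equal use they are 8–12%.

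**Would a threshold help?** For ten tests at 5%, 1 − 0.95^10 = 40.1%, and the simulations give 37–41%. Bonferroni at 0.05/10 gives 4–5%. A minimum count alone does not help: with at least 20 users, mixed use and N = 420, some set still comes top in 98–99% of null data sets.

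**Would the hold-out help if it had a pass level?** Against 50% chance in 84 patients, requiring at least 51 correct passes falsely in 3.1%. Requiring merely more than half correct (43 or more) passes falsely in 46%. Even the stricter gate concerns the model as a whole, not a named acupoint.

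**The case against.** Four arguments weigh against the point.

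1. A reader might infer that the plan ranks combinations and takes the top one. The article describes no ranking and no such rule. It describes prediction of responders and of suitable points for individual patients. This stands, so the naming rates above hold only if leading model features are reported as best. The article's superlatives make that a natural outcome, and it states no other selection criterion.

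2. A reader might infer that the study cannot return a negative answer. That goes too far, because chance-level performance in the hold-out would be a visible negative result. It is an indirect one, though: no level is fixed, only FD patients are covered, and good performance would not show that acupoints matter. The article also plans no effect size for a selected acupoint, so an inflated estimate is a risk if one is reported, not a stated intention.

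3. A reader might infer that the winner will usually be a rarely used combination. This is supported only for whole sets compared on raw response without an adequate minimum count or shrinkage, and the article does not fix that coding.

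4. Thresholds, penalties and multiplicity control often sit in a full protocol or analysis plan that is not shown here. That is true of the details. But the article itself sets out predictors, algorithms, responder concept, split and performance measures, and that stated chain does not support its stated conclusion.

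The simulations have limits too. No support vector machine was run. Independent use is unrealistic when pattern identification guides the choice of points. The pair contrast and its cut-offs are not the plan's.

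**Conclusion.** The point holds in a bounded form. The article commits to identifying the most effective acupoints, and the validation it describes does not test that claim. Followed as written, the plan could report best acupoints when all are equivalent. If leading model features are so reported, the false signal has a median odds ratio of about 1.3 to 1.9 for the top single point, and 16 to 22 percentage points for the best pair before validation. These sizes rest on assumed use rates, responder rates and independent use. Correlated use would change them and reduce the number of distinct sets. The mismatch between conclusion and check depends on none of these assumptions. The weakness is correctable before analysis and does not affect the descriptive first aim.

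**What to change.** In section 2.6, state a selection rule that can return no acupoint:

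- **Candidates.** Single acupoints and pairs used by a stated minimum share of patients, fitted with a penalised model. As an illustration, 10% is 42 of 420.
- **Evidence.** Call a point or pair effective only if it exceeds a multiplicity-controlled null. One option is a permutation of the whole selection procedure using the maximum statistic, with clinic and pattern handled by model adjustment or coarse strata. Permuting within every clinic-by-pattern cell is not practical: 15 × 6 = 90 cells leave 420 / 90 = 4.7 patients each. The simpler option is Bonferroni or Holm over the candidates. With all ten printed points and 45 pairs, the Bonferroni level would be 0.05 / 55 = 0.0009.
- **Estimation.** Report the selected acupoint's effect, with its interval, only from held-out or out-of-fold data.
- **Conclusion.** If nothing passes, conclude that no acupoint or combination was distinguishable from the others, and label any listing hypothesis-generating.

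Accuracy, sensitivity and specificity can stay as measures of the responder model.

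**Cost.** Wording and computing time, with no new patients or data. Rare combinations are not assessed, power to name an acupoint falls, and the study may report that none was found. A single hold-out is also imprecise. With 84 patients, 42 users and 42 non-users, and 50% response (all favourable assumptions), the 95% half-width is 1.96 × √(0.25 × 2/42) = 21 percentage points. This favours out-of-fold estimation.

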#### 2.3.5. Pattern identification types of patients.

Patients will be categorized into 6 pattern identification types, as per the clinical practice guideline of Korean medicine for FD: spleen and stomach deficiency and cold pattern; spleen deficiency with qi stagnation pattern; liver-stomach disharmony pattern; tangled cold and heat pattern; pattern of dampness and heat in the spleen and stomach systems; and food retention pattern. The Standard Tool for Pattern Identification of Functional Dyspepsia (STPI-FD) questionnaire will be employed to determine the patient pattern.^[13]^ This questionnaire consists of 12 categories of questions reflecting various symptoms of FGIDs. This questionnaire will be presented to patients only once at the first visit (0 weeks).

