### 2.4. Intervention

Acupuncture will be used to treat all FGID patients as determined by the doctor. Patients may receive extra treatment depending on the doctor decision.

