#### 2.4.2. Other co-interventions.

Herbal acupuncture, herbal medicine, cupping therapy, moxibustion, and other treatments will also be provided simultaneously in clinics in addition to traditional acupuncture. Co-interventional data will be considered a covariate when estimating the impact of the treatment.

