Next, the best acupoints for treating FGID with acupuncture will be predicted using machine learning and the patient results. Individuals respond to acupuncture in different ways.^[18]^ As mentioned above, machine learning can be used to forecast the best acupoints based on patient outcomes. In a previous study, the effectiveness of acupuncture was predicted using a support vector machine for individuals with FD.^[11]^ Gender, disease subtype, and education level were significant predictors of treatment results. Similarly, machine learning will be used to identify those who are more likely to respond to acupuncture, or those who will improve (display minimally clinically significant differences) from baseline following 4 weeks of acupuncture treatment. Data from 80% of the patients with FD will be used to create a predictive model, and the data from the other 20% will be used to validate the model and assess its performance. The performance of supervised machine learning models, such as support vector machine and logistic regression models, will be assessed using accuracy, sensitivity, and specificity analyses. Machine learning can be used to predict the optimal acupoints for each patient and help doctors assess treatment responses.

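### The stated acupoint model names no adjustment for pattern, baseline score or clinic, although pattern guides acupoint choice, so inert acupoints can appear effective or harmful

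*Protocol article*

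**What the plan says.** All references are to the protocol article.

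- **Who chooses the treatment (2.4):** "Acupuncture will be used to treat all FGID patients as determined by the doctor". There is no randomisation.
- **What guides the choice (2.4.1):** "Pattern identification will be used to choose the acupoints, and more acupoints will be permitted based on the patient additional symptoms".
- **What is recorded on pattern (2.3.5):** "Patients will be categorized into 6 pattern identification types, as per the clinical practice guideline of Korean medicine for FD". The STPI-FD questionnaire assigns the pattern once, at week 0.
- **Outcome in the analysis (2.6):** "Each outcome measure will be compared to the clinical outcome between the baseline and termination, and the clinical outcome will be a dependent variable".
- **Predictors in the analysis (2.6):** "Combinations of the applied acupoints will act as independent factors to predict the most effective acupoints for the acupuncture treatment".
- **Named covariate (2.4.2):** "Co-interventional data will be considered a covariate when estimating the impact of the treatment".
- **Pattern in the Discussion (3):** "Depending on the pattern identified, supervised learning will be used to extract important clinical features".
- **Earlier FD work cited in the Discussion (3):** "Gender, disease subtype, and education level were significant predictors of treatment results".

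The Discussion defines responders by improvement from baseline after 4 weeks. It builds the prediction model on 80% of the FD patients and tests it on the other 20% by accuracy, sensitivity and specificity.

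**The concern.** The article says that the indication determines the exposure, and then states a model of exposure on outcome whose named terms do not include the indication. From that model it intends to name the best or most effective acupoints. This is the set-up for confounding by indication. If patients with one pattern recover more readily than others, the acupoints preferred for that pattern inherit the better prognosis, whether or not they do anything.

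Baseline score raises a related problem. A change from baseline uses the baseline value but does not adjust for it. Patients who start worse tend to improve more through regression to the mean, and any acupoint used more often in them takes the credit. Clinic matters in the same way if the 15 clinics differ both in point selection and in outcome.

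At stake is the main output of the registry, a list of acupoints meant to guide practice. The 20% hold-out does not protect it. The held-out patients come from the same clinics and the same selection habits, so a confounded association predicts just as well in them.

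**Working it through.** The article has no figure to reproduce. The 420 patients are justified by outpatient volume, and no association strengths are given. The check asks how far an inert acupoint can be pushed from an odds ratio (OR) of 1. Every strength below is an assumption.

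**Inputs from the article:** 420 patients; 15 clinics (420/15 = 28 each on average); 6 patterns; 10 example acupoints; an 80% training share (0.8 × 420 = 336 at most, if every patient had FD).

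**Closed form.** Take two pattern groups of equal size. The acupoint is used in a fraction a of the first and b = 1 − a of the second. The groups respond at rates r1 and r0 whatever the acupoint. Overall use is 50%, so

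- response among users = a·r1 + (1 − a)·r0
- response among non-users = (1 − a)·r1 + a·r0

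1. Use 60%/40%, response 55%/45%: users 0.6 × 0.55 + 0.4 × 0.45 = 0.51, non-users 0.49. OR = (0.51/0.49)² = 1.08.
2. Use 70%/30%, response 60%/40%: users 0.7 × 0.6 + 0.3 × 0.4 = 0.54, non-users 0.46. OR = (0.54/0.46)² = 1.38.
3. Use 80%/20%, response 65%/35%: users 0.8 × 0.65 + 0.2 × 0.35 = 0.59, non-users 0.41. OR = (0.59/0.41)² = 2.07.
4. Equal response (50%/50%), any use: OR = 1.00.

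The chance of p < 0.05 (two-sided test, counting only the tail in the direction of the bias, so 2.5% when there is no bias) is 6% in case 1 at either sample size. It is 31% (n = 336) and 37% (n = 420) in case 2, and 91% and 96% in case 3.

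**Simulation with ten inert acupoints** (300 runs per row, n = 420, 15 clinics, 6 patterns, logistic model). Acupoint use varies by pattern and by clinic with SD 1 on the logit scale (1.5 in the last row). Entries are the share of inert acupoints significant at two-sided 0.05.

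| Pattern SD on outcome | Clinic SD on outcome | Acupoints only | + pattern | + pattern and clinic |
|---|---|---|---|---|
| 0 | 0 | 4.7% | 5.2% | 5.6% |
| 0.5 | 0 | 9.2% | 5.7% | 5.3% |
| 1 | 0 | 18.0% | 5.3% | 5.9% |
| 0.5 | 0.5 | 11.1% | 7.7% | 6.2% |
| 1 | 0.5 | 17.5% | 7.8% | 6.5% |
| 1 | 1 | 23.6% | 14.1% | 6.1% |

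In the five rows with an outcome association, at least one of the ten acupoints was falsely significant in 61% to 93% of runs with acupoints only, and in 43% to 49% with pattern and clinic added. That remainder is ordinary multiplicity over ten tests. A separate, milder ten-acupoint setting, in which use across patterns was unrelated to prognosis, gave 8.3% per acupoint against 5.5% adjusted.

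**Full alignment.** One inert acupoint is used in 20% to 80% of patients across the six patterns, in line with a prognosis from −0.4 to +0.4 SD. Two separate simulations (400 and 1,000 runs, n = 420) gave an unadjusted OR of 1.40 and 1.42, and false positives in 40% and 42%, against 5.5% and 6% with pattern added.

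**Severity-driven use.** With use of 60% above and 30% below median severity, the unadjusted OR was about 1.5. I leave this out of the range. The article does not state that severity drives choice, and the comparison that was run changed both the outcome (responder to week-4 score) and the adjustment, so it does not isolate the missing baseline term.

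**The case against.** The strongest reply is that this is a condensed article, that covariate lists are commonly left to an analysis plan, and that section 2.6 does not say the acupoints are the only inputs. The Discussion ties supervised learning to the identified pattern, cites patient characteristics as predictors, and aims at optimal acupoints for each patient, which suggests patient-level features. This stands in part. A reader might infer that the plan excludes pattern outright, and the text does not support that. But the Discussion does not say whether pattern is a covariate, a stratifier or a separate analysis. Section 2.6 already fixes the predictors, the outcome and the conclusion to be drawn, so the point concerns what is stated and not only what is absent.

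Four further limits stand.

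- Only pattern and additional symptoms are stated as guiding acupoint choice. That severity, subtype or clinic also does so is plausible but inferred.
- The prediction model in the Discussion uses FD patients only. FD versus IBS is constant there and cannot confound it, although section 2.6 speaks of FGID patients as a whole.
- The simulations count p-values for single acupoints at n = 420. The article judges models by accuracy, sensitivity and specificity, and the training set is at most 336. The error rates therefore illustrate the bias and do not forecast the planned output.
- A reader might infer that, because every patient receives acupuncture, nothing can be compared. That does not follow, since patients who received a given point are compared with those who did not.

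**Conclusion.** The point holds as a matter of what can happen. Acupoint choice depends on pattern by the article's own account, the stated acupoint model names only co-interventions as a covariate, and baseline score and clinic have no stated role as adjusters. Associations from that model cannot be read as effectiveness.

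The size depends wholly on assumed strengths. The OR for an inert acupoint runs from 1.0 (no link between the factor and outcome) to about 2 (strong link). The false-positive rate is about 8% to 24% in the multi-acupoint settings with mild to strong links and about 40% under full alignment, against about 5% to 7% once the factors involved are in the model. Adding pattern alone is not enough if clinic also affects outcome (about 8% to 14%).

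A reader might go further and conclude that inert acupoints will look effective, or that the results will mostly reflect who receives which points. The article does not support that: if the factors are unrelated to outcome, the acupoints-only model keeps its nominal 5%.

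**What to change.** In section 2.6:

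1. Name a base model with baseline score of the same instrument, STPI-FD pattern, disease subtype (FD/IBS where both are modelled, epigastric pain/postprandial distress within FD), age, sex, acupuncture expectancy, co-interventions and clinic. Enter these as covariates in the logistic acupoint model and as input features in the support vector machine.
2. Add the acupoints to this base model and report what they contribute out of sample beyond it.
3. Describe the results as acupoints associated with improvement and hypothesis-generating, not as best, optimal or most effective. This wording is needed even after adjustment, because additional symptoms also guide the choice and the recorded variables may capture them only in part.

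**Cost.** Pattern, baseline scores, expectancy, co-interventions, subtype and clinic are already collected or known; I assume that age and sex are on the case report form. The analysis grows slightly and the claim becomes more modest. The extra parameters are a real load. Pattern (6 − 1 = 5) and clinic as indicators (15 − 1 = 14) add 19 terms, with at most 336/15 = 22.4 training patients per clinic on average. The article gives no basis for calculating a change in sample size, and none is proposed.
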